### Exploring the synergy of clinical data with breath sounds

Clinical data will be explored for its predictive capacity in the above tasks and added to the breath sound analysis either as a support vector machine (SVM) or in conditional feature extraction upstream of the neural network.

## Clinical assessment of lung auscultation and LUS

The following data will be reviewed by external experts and interpreted using standardised report forms noting the binary presence/absence of several anomalies as well as a text field for other notable observations: routine chest X-ray films (usually 2 incidences, posterior-anterior and lateral); lung auscultation audio clips (10 anatomic regions represented, 30 s recordings of each region); and LUS images (10 anatomic regions represented, 5 s video clips of each region). The analysis will be blinded and the assessor will not have any knowledge of the linked clinical data or association between the various imaging modalities (i.e., IDs are scrambled between media sources and chest X-ray images will be reviewed blinded to the patient’s LUS images, auscultation audio, clinical data, etc.). These blinding and standardisation procedures are expected to minimise performer and study management bias respectively.

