### Hypothesis and objectives

#### Primary hypothesis

We hypothesise that point-of-care digital lung auscultation and LUS have a clinically exploitable predictive performance for the detection of pathological acoustic and sonographic signatures in patients with ILD. Furthermore, we propose that these signatures are sufficiently unique to not only discriminate ILD patients from control subjects, but also from COPD and other respiratory diseases, and perhaps even to categorise the various severity grades and subtypes of ILD, when determined. We further hypothesise that the automated interpretation of lung auscultation and LUS by deep learning could match or outperform expert evaluation and standardise lung auscultation and LUS interpretation.

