### Primary and secondary outcomes

The primary outcome is the diagnostic of ILD, both IPF and NSIP, versus control subjects or COPD. We will assess the predictive performance of the *DeepBreath* algorithm-evaluated lung auscultation and LUS in the following identification and risk stratification tasks as follows: (1) to discriminate ILD from control subjects (according to expert clinical diagnosis [42]); (2) to differentiate ILD from COPD; (3) to predict ILD clinical severity (according to a HRCT grading scale^1^ and lung function tests^2^); and (4) to differentiate the subcategories of ILD (such as IPF, NSIP) according to the gold standard diagnosis [2, 43, 44]).

Secondary outcomes are the clinical, functional and radiological characteristics of IPF, NSIP and COPD diagnosis. We will: (1) compare the predictive performance of human, expert-identified acoustic and LUS signatures in the above predictive tasks (Kappa coefficient); (2) assess diagnostic performance of a model trained to detect crackles; (3) explore the utility of adding clinical data (signs, symptoms, demographics, medical history and basic paraclinical tests) to the breath sound algorithms; and (4) determine the impact of the diseases on subjects’ health-related quality of life measured with the standardised King’s Brief Interstitial Lung Disease (K-BILD) [47], the COPD assessment test (CAT) [48], and the 36-item Medical Outcomes Study Short-Form Health Survey (SF-36) [49] severity assessment questionnaires.

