### Statistical analysis plan

For descriptive statistics related to the clinical data collected, all continuous variables will be reported as medians with their interquartile ranges. Binary and categorical variables distribution will be reported as proportions and percentages. To evaluate baseline demographic differences and outcomes differences between the case and control patients, conditional logistic regressions will be used to account for the matched design. Pearson’s and Spearman’s correlation coefficients will be used to assess the relationship between continuous variables normally and non-normally distributed, respectively. For the primary outcome, each task will be quantified using descriptive statistics (i.e., proportion and type of abnormalities), as well as the AUROC, sensitivity, specificity, positive predictive value, negative predictive value, and likelihood ratios (with 95% CIs over a fivefold cross-validation).

The diagnostic accuracy of each echographic sign will be assessed and sensitivity, specificity, positive predictive value, negative predictive value, positive likelihood ratio, and negative likelihood ratio with their 95% CIs will be calculated. To find the combination of echographic signs with the best diagnostic accuracy, we will compare the performance of several multivariable models, such as logistic regression, random forest and neural networks. Performance will be reported on a test set comprising 20% of the data in a tenfold cross-validation with 95% CIs. As a secondary objective, we will aim to compare the predictive performance of human expert-identified acoustic signatures in the above predictive tasks. First, we will describe the expert labels by the percentage of sound labels attributed to each diagnosis. A multivariable logistic regression will be derived using the clinical data and sound labels to estimate the diagnoses, as for the primary objective. A kappa score will be used to assess the concordance between *DeepBreath* and expert diagnosis consolidated into a basic predictive model.

The K-BILD, CAT and SF-36 questionnaires will be analysed with descriptive statistics. Associations between the questionnaires’ sum scores and lung function parameters will be quantified by Spearman’s rank correlation coefficient. We will consider correlations < 0.3 as negligible, ≥ 0.3 to < 0.5 as low, ≥ 0.5 to 0.7 as moderate, and ≥ 0.7 as strong.

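### The plan hypothesises that DeepBreath matches or outperforms experts, but compares it, by kappa, with a regression on clinical data and expert sound labels rather than with an expert's reading of the patient

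*Protocol article*

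**What the plan says.** All places are in the protocol article.

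- **Primary hypothesis:** automated interpretation of auscultation and lung ultrasound (LUS) "could match or outperform expert evaluation and standardise lung auscultation and LUS interpretation".
- **Clinical assessment of lung auscultation and LUS:** external experts review chest films, audio clips and LUS clips on "standardised report forms noting the binary presence/absence of several anomalies as well as a text field for other notable observations". They are blinded: "the assessor will not have any knowledge of the linked clinical data or association between the various imaging modalities".
- **Primary and secondary outcomes:** the first secondary outcome is to "compare the predictive performance of human, expert-identified acoustic and LUS signatures in the above predictive tasks (Kappa coefficient"). No other measure is named for it.
- **Statistical analysis plan:** the labels are first summarised ("we will describe the expert labels by the percentage of sound labels attributed to each diagnosis"). Then: "A multivariable logistic regression will be derived using the clinical data and sound labels to estimate the diagnoses, as for the primary objective". Then: "A kappa score will be used to assess the concordance between *DeepBreath* and expert diagnosis consolidated into a basic predictive model".

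The expert clinical diagnosis named under the primary outcome is the reference standard. It is not the output of the blinded readers.

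**The concern.** A claim to match or outperform experts needs two things: the experts' own verdict on each patient, and a measure that shows which side is closer to the reference diagnosis. As described, the plan supplies neither. The readers mark findings, a fitted model turns these into a diagnosis, and the measure named is agreement between that model and DeepBreath.

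At stake is the interpretation of the result. DeepBreath could agree well or poorly with this model, or even be more accurate than it, and a reader would still not know how it compares with the people who read the same clips. The primary accuracy estimates for DeepBreath against the reference diagnosis are not affected.

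**Working it through.** The article states no sample size, power or margin for a comparison with experts, so there is no planned figure to reproduce. The check has three parts.

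**1. Does the comparator represent the experts?**

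| | Blinded reader | Planned regression |
|---|---|---|
| Clinical data | withheld | included |
| Audio | heard in full | as labels |
| LUS | seen in full | not named as an input |
| Output | findings and free text | estimated diagnosis |

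- *Something is added.* The regression may score well because of clinical data the reader never had. It is also not like for like with a DeepBreath that uses sounds or images alone.
- *Something may be lost.* The Background section relies on the timing of crackles within inspiration, and the LUS section on the spacing of B-lines. A presence/absence mark need not carry these.
- *Something is left out.* The hypothesis and the secondary outcome cover LUS signatures, while the regression in the analysis section names sound labels only.

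The first effect can raise the comparator and the other two can lower it.

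**2. Can kappa show a match or an advantage?**

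Inputs: 80 ILD and 40 controls (Sample size calculation). The accuracies below are assumptions, because the article gives none for either side. Errors are taken as independent within true class, and sensitivity equals specificity.

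Kappa = (po − pe)/(1 − pe), where po is observed and pe is chance agreement. For 0.90 against 0.70:

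- both positive: (80 × 0.9 × 0.7 + 40 × 0.1 × 0.3)/120 = 51.6/120 = 0.43
- both negative: (80 × 0.1 × 0.3 + 40 × 0.9 × 0.7)/120 = 27.6/120 = 0.23
- po = 0.43 + 0.23 = 0.66
- positive rates: 76/120 = 0.633 and 68/120 = 0.567
- pe = 0.633 × 0.567 + 0.367 × 0.433 = 0.518
- kappa = (0.66 − 0.518)/(1 − 0.518) = 0.295

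Swapping the two sides leaves every term unchanged.

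| DeepBreath | Expert model | Kappa |
|---|---|---|
| 0.90 | 0.70 | 0.295 |
| 0.70 | 0.90 | 0.295 |
| 0.95 | 0.75 | 0.421 |
| 0.75 | 0.95 | 0.421 |
| 0.90 | 0.90 | 0.612 |
| 0.99 | 0.80 | 0.559 |

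The last two rows show that a much better DeepBreath can give a lower kappa than two equal classifiers.

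**3. What could a direct paired comparison show at this size?**

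For equal sensitivity s on both sides and independent errors, the discordant proportion is 2s(1 − s). The 95% half-width of the paired difference is 1.96 × √(2s(1 − s)/n).

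- Sensitivity, n = 80 ILD: 1.96 × √(0.32/80) = 0.124 at s = 0.80, and 1.96 × √(0.18/80) = 0.093 at s = 0.90.
- Specificity, n = 40 in the comparison group: 0.175 at 0.80 and 0.131 at 0.90.

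Errors that coincide on the same patients would narrow these intervals. Under independence, McNemar power at two-sided 5% in the 80 ILD patients is about 88% for 0.90 against 0.70, 42% for 0.90 against 0.80, and 13% for 0.85 against 0.80.

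**The case against.** **The form is not reproduced.** One sentence of a journal article covers three modalities, and a diagnosis field may exist in the full form. The analysis wording "expert diagnosis consolidated into a basic predictive model" could also be read as experts' own diagnoses being combined. This stands in part: one cannot say that the experts never give a diagnosis. But none is described, the free-text field has no stated use in the analysis, and the sentence just before that wording describes a regression on labels and clinical data.

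**The plan sets out to compare signatures, not overall impressions.** The secondary outcome speaks of signatures identified by experts, and modelling the labels as for the primary objective may mean that AUROC, sensitivity and specificity will be reported for the label model too. That is fair, and such a display would be useful. It would still describe a regression, and part of its performance would come from the clinical data. The hypothesis speaks of expert evaluation.

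**It is a pilot, and the hypothesis says only that the algorithm could match or outperform.** This argues against demanding a powered test. It does not make agreement a measure of relative accuracy.

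**Stronger readings to avoid.** A reader might infer that the regression handicaps the experts through estimation error, so that DeepBreath would look better than it is. The document does not support this. The loss depends on the number of uninformative labels and on shrinkage, and neither is stated. The planned model is called basic, DeepBreath's own last stage is also a logistic regression, and the clinical data may push the comparator upward. Nor does it follow that the pattern across sites is lost, since marks recorded site by site would keep it.

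**Conclusion.** The concern holds for the plan as described. The hypothesis of matching or outperforming expert evaluation is not tested, because the comparator is a model that mixes clinical data with expert sound labels and the measure named for the comparison is symmetric.

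The symmetry of kappa is exact and needs no assumption; the kappa values are illustrations. The direction and size of any bias in the comparator cannot be determined from the document. The conclusion assumes that the report forms hold no patient-level diagnosis beyond what the article describes. If they do, the remaining defect is that the analysis does not score that diagnosis directly. This should be changed before the readings are made, but it does not touch the primary accuracy estimates.

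**What to change.** 1. Add one item to the audio form and one to the LUS form. After all 10 sites of a patient, the blinded reader classifies the patient, at least as ILD, COPD or neither, and as IPF or NSIP if ILD, with graded confidence.
2. Score this reading against the reference diagnosis beside DeepBreath's out-of-fold result on the same patients and the same modality. Report paired differences in AUROC, sensitivity and specificity with 95% CI. Kappa may stay as a description of agreement. Given the half-widths above, present this as estimation; a claim to match would need a margin fixed in advance.
3. Keep the label model as a secondary analysis. Where it is meant to represent the experts, fit it without clinical data, and do so for LUS labels as well as sound labels.
4. If no patient-level reading is collected, restate the hypothesis as agreement with a model built on expert labels.

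Cost: slightly more time from readers already engaged. The clips of one patient must stay together within a modality; the article scrambles identifiers between media sources, so this appears compatible with the blinding. Recordings are stored, so no patient need be contacted again. The item asks for a call without clinical context, which is narrower than ordinary expert practice and should be reported as such.

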## Pulmonary function tests and chest CT scan

For all subjects, spirometry, body-plethysmographic parameters (see details above) and lung diffusion capacity for carbon monoxide (TLco/Kco) will be measured. Participants’ lung images recorded from previous HRCT (or X-rays) during past routine visits will be used. No chest CT scans will be performed as part of this study; only lung images of participants previously recorded as part of their regular follow-up or to be performed in this context will be used. The presence on the chest CT scan of honeycombing, traction bronchiectasis, reticulations, ground-glass opacities, and emphysema will be measured for patients with IPF, NSIP or emphysema. The main chest CT scan features of IPF are reported to be basal and peripheral reticulations, traction bronchiectasis, minimal ground glass opacities, and moderate or extensive honeycombing. For NSIP, the CT scan typically demonstrates bilateral lung involvement and invariably some extent of ground-glass opacities, mainly in the lower zones with fibrotic changes, while honeycombing is not a common feature [55]. The presence on the chest CT scan of structural abnormality, such as ≥ 5% emphysema and/or ≥ 15% gas-trapping and/or airway wall thickness ≥ 2.5 mm [56], will be measured for patients with COPD. The protocol assumes normal lung parenchyma in the control group, which will not be exposed to radiation unless controls have already undergone a recent (i.e., < 5 years) chest CT scan for other reasons. This will be taken into consideration as we will investigate the association of lung sounds with radiological characteristics.

## Questionnaires

Demographics including age, sex, ethnicity, environment (smoking status, long-term exposure to occupational or environmental agents, etc.), treatments, presence of chronic respiratory symptoms or repeated lower respiratory tract infectious diseases, as well as a diagnosis of other comorbidities (obesity, immunodeficiency, alpha-1 antitrypsin deficiency, etc.) will be reported in a questionnaire (Additional file 1). Severity of functional limitations according to the New York Heart Association (NYHA) functional classification [57] will be also reported if available.

The impact of IPF and NSIP on subjects’ health-related quality of life will be measured with the standardised K-BILD questionnaire [47] (use with license agreement), which covers 15 questions exploring 3 health dimension scores (psychological, breathlessness and activities, and chest symptoms) using a 7-point Likert response scale (scores range from 0 to 100, a higher score indicating better health status). The impact of COPD will be assessed with the CAT [48] (use with license agreement) that measures eight items: cough; phlegm; chest tightness; breathlessness; limited activities; confidence leaving home; sleeplessness; and energy. Scores range from 0 to 40, with a higher score indicating a more severe impact of COPD on a patient’s life. The SF-36 will also be used to assess the impact of IPF, NSIP or COPD on patients’ quality of life. The investigators will double-check on-site that the questionnaires are fully and accurately completed. Data collection will be carried out using the online REDCap database (REDCap, Vanderbilt University, Nashville, TN, USA; https://www.project-redcap.org/resources/citations/). Conditions or complaints occurring after enrolment will not be considered in the statistical analyses. Current symptoms at enrolment will be registered.

### Sample size calculation

Each patient will provide 10 audio recordings of 30 s. Samples will be considered at the patient level with all 10 recordings. In deep learning, sample size calculation is an intractable problem that is usually discovered through empirical investigation. The number of samples required to reach a certain performance criterion is dependent on the characteristics of the dataset, the diversity and number of the classes, the degree of data augmentation possible, as well as the complexity of the learning algorithm. Thus, sample size calculations cannot rely on the traditional statistical heuristics that are often used in biostatistics. Rather, sample size estimations in deep learning are mostly made by analogy. Evaluating existing knowledge on similar datasets, we find that the expected proportion of velcro-like crackles in IIP patients is nearly 100% [4], whereas the prevalence of coarse crackles is 71% in COPD patients [58]. The exclusivity of these sounds among groups is not known, but overlap is assumed to be minimal and pathological sounds are by definition absent in non-ILD and non-COPD control subjects. Assuming a similar discriminative power compared to a previous work done by our group (personal communication) to distinguish between normal and pathological lung sounds in pneumonia from 80 patients in balanced classes (40 pathological; 40 controls) with 8 auscultation sites of 30 secs each, we estimate using the same number of patients in each class to achieve convergence at above 80% of the area under the receiver operating characteristic curve (AUROC). Thus, we will aim to enrol at least as many patients in each group: 80 ILD (40 IPF, 40 NSIP); 40 COPD; and 40 controls (i.e., known not to have ILD or COPD, and with normal lung function). As the recruitment site would expect 120 ILD patients (40% with IPF; 60% with NSIP) and 100 with COPD over the space of one year, this number is achievable in the time frame of the study (6 months), even with a 70% consent rate.

This sample size is also predicted to be sufficient for deep learning on LUS. Our preliminary results (personal communication) on COVID diagnosis using deep learning achieved 90% AUROC with 150 patients (balanced classes of 75 COVID + and 75 COVID-). As human experts cannot perceive a COVID-specific signature in LUS with high specificity, this is likely a more technically difficult task than distinguishing ILD and COPD from healthy patients. Indeed, there is ample evidence on the visible signs of ILD on LUS [59].

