### Study procedure

The study will be performed over a period of 6 months. Recruitment can be stopped before the anticipated end if the inclusion of 160 patients is reached before. A trained research nurse/doctor ([name]) will recruit the subjects during a single routine consultation in the outpatient clinic. This will include checking the selection criteria for each patient prior to study participation, obtaining written informed consent, administering questionnaires on demographic characteristics (age, sex, occupation, long-term exposure to occupational or environmental agents, etc.), relevant medical history, and symptomatic presentation (Additional file 1), which will be captured by an electronic case report form to be completed by the study coordinator on a tablet. The nurse/doctor will also administer the standardised K-BILD [47], CAT [48], and SF-36 [49] severity assessment questionnaires, and record lung sounds during 5–7 min with an electronic stethoscope in the same zones as LUS acquisition, as previously proposed by our group [40]. For the LUS examination using a standard point-of-care ultrasound device, an adapted version of our previous 10-point acquisition protocol [50] will be used, which involves scanning the anterior superior, anterior inferior, posterior superior, posterior inferior and lateral thorax regions. In addition, pulmonary functional tests (conducted with patients in a stable condition) will be collected, as well as chest X-rays with two incidences (posterior-anterior and lateral) and HRCT scans for IIP patients (within 12 months). Controls will not be exposed to a chest X-ray and/or CT scan unless required as part of their routine follow-up; cases will have undergone such imaging given that it is part of their diagnostic evaluation.

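### The stated patient numbers do not support enrolling 40 IPF, 40 NSIP and 40 COPD patients in 6 months at 70% consent; the IPF target fails on every reading of them

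*Protocol article*

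**What the plan says.** The section on sample size calculation in the protocol article aims for 80 ILD patients (40 IPF and 40 NSIP), 40 with COPD and 40 controls. The size comes by analogy from earlier work with 40 patients per class, from which the authors expect an AUROC above 80%.

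For feasibility, the same section says that "the recruitment site would expect 120 ILD patients (40% with IPF; 60% with NSIP) and 100 with COPD over the space of one year", and concludes that "this number is achievable in the time frame of the study (6 months), even with a 70% consent rate". No working is shown.

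The section on study procedure fixes the same window: "The study will be performed over a period of 6 months". It provides for an early stop: "Recruitment can be stopped before the anticipated end if the inclusion of 160 patients is reached before". The article mentions no extension, no second site and no separate 6-month patient count.

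**The concern.** The inputs are counts over one year, while the conclusion is about half a year and is further reduced by 30% non-consent. The IPF count is only 48 for a whole year, so a target of 40 leaves little room before either reduction is applied.

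The 40-per-class size is the article's only rationale for the auscultation models, and the next paragraph relies on the same size for lung ultrasound. If a class cannot reach 40 in the stated window, the analogy no longer covers the contrasts that use it. The most exposed is IPF versus NSIP, the fourth task under the primary outcome, because it uses the two smallest expected yields and nothing else.

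**Working it through.** **Inputs (sample size calculation; the 6 months also in study procedure)**

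- ILD: 120 per year, 40% IPF and 60% NSIP, so 120 × 0.40 = 48 IPF and 120 × 0.60 = 72 NSIP per year.
- COPD: 100 per year.
- Consent 70%, window 6 months, target 40 per disease group.

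Expected enrolment = annual count × fraction of the annual count seen in the window × consent rate.

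**Trying to reproduce the plan's conclusion**

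| Reading | IPF | NSIP | ILD together | COPD |
|---|---|---|---|---|
| Target | 40 | 40 | 80 | 40 |
| Even arrival, 6 months, 70% consent | 48 × 0.5 × 0.7 = 16.8 | 72 × 0.5 × 0.7 = 25.2 | 42.0 | 100 × 0.5 × 0.7 = 35.0 |
| Even arrival, 6 months, 100% consent | 24 | 36 | 60 | 50 |
| Whole annual pool seen in 6 months, 70% consent | 48 × 0.7 = 33.6 | 72 × 0.7 = 50.4 | 84.0 | 70.0 |

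No row at 70% consent gives 40 in all three groups. The last row clears the pooled ILD target of 80 and the COPD target, but not IPF. Under that reading, if each of the 48 IPF patients consents independently with probability 0.7, the chance that at least 40 do is 0.027 (binomial).

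**Consent needed to reach 40 in 6 months, even arrival:** IPF 40/24 = 167%, NSIP 40/36 = 111%, COPD 40/50 = 80%. The first two are impossible.

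**Months needed at 70% consent, even arrival of new patients:** 40/(annual × 0.7) × 12, giving IPF 14.3, NSIP 9.5 and COPD 6.9.

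**Effect on precision.** The article states no interval, so this assumes AUROC = 0.80 and the Hanley-McNeil standard error:

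SE² = [A(1−A) + (m−1)(Q₁−A²) + (n−1)(Q₂−A²)] / (mn), with Q₁ = A/(2−A) = 0.667 and Q₂ = 2A²/(1+A) = 0.711. The 95% CI is A ± 1.96 SE. The first-named group is m.

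| Contrast | Sizes | SE | 95% CI |
|---|---|---|---|
| IPF v NSIP, planned | 40 v 40 | 0.050 | 0.70-0.90 |
| IPF v NSIP, even arrival | 17 v 25 | 0.074 | 0.66-0.94 |
| IPF v NSIP, pool | 34 v 50 | 0.052 | 0.70-0.90 |
| ILD v controls, planned | 80 v 40 | 0.040 | 0.72-0.88 |
| ILD v controls, even arrival | 42 v 40 | 0.049 | 0.70-0.90 |

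The last row takes 40 controls as enrolled; no control flow is stated, so that cannot be checked. The exclusion criteria would lower all yields further, but no exclusion rate is given and none is applied.

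**The case against.** The strongest reply is that halving the annual counts is itself an assumption. The cases are outpatients already diagnosed and enrolled at a routine consultation, so many may attend more than once a year, and the number seen in 6 months need not be half the number seen in 12. No visit frequency is given. This stands: the NSIP and COPD shortfalls are conditional on even arrival, and the COPD gap is small even then. It does not rescue IPF, which reaches only about 34 when the entire annual pool is granted.

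Four stronger readings are tempting, and the document does not support them.

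- *The authors forgot to halve an annual figure.* The unhalved ILD figure at 70% (84) does clear 80, so this is plausible, but no working is shown. It would not explain IPF, which misses even over a full year at 70%.
- *The early-stop rule lets COPD patients and controls take IPF places.* The rule counts 160 in total, but under even arrival only 16.8 + 25.2 + 35 = 77 cases accrue in 6 months, with COPD below its own target. The rule would come into play only if 160 − 77 = 83 controls enrolled, against 40 planned. The wording is also permissive, and the sample size section sets a minimum for each group.
- *Every ILD contrast becomes much less precise than stated.* The article states no precision, and ILD versus controls goes only from SE 0.040 to 0.049, about a quarter wider.
- *Recruitment simply needs 14 to 15 months.* That holds only for a steady flow of new patients. With a recurring pool of 48, more time largely re-approaches the same people.

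It is also fair to say that the article calls the sample modest and the study a pilot, and lists the IPF-NSIP distinction among its objectives only as a possibility. That limits the harm but does not make the feasibility statement correct.

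**Conclusion.** The feasibility sentence is not supported by the figures in the same sentence. The IPF target of 40 is missed on every reading, with an expected yield between about 17 (even arrival) and 34 (whole pool seen). NSIP (25 to 50) and COPD (35 to 70) depend on which reading is right: both miss under even arrival at 70% consent, and both are met under the pool reading.

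The material consequence is confined mainly to IPF versus NSIP, and it ranges from a clear loss of precision under even arrival to almost none under the pool reading. The yields rest on the stated counts, subtype split and 70% consent applied equally to all groups; the intervals rest on the assumed AUROC of 0.80. The IPF conclusion does not depend on the arrival pattern.

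**What to change.** Replace the feasibility sentence. First state whether the annual counts are a flow of different patients or a follow-up pool, and what share of them is expected to attend within 6 months. Then take one of two routes:

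1. Keep 6 months and state the attainable sizes at 70% consent, capped at target: IPF about 17 to 34, NSIP 25 to 40, COPD 35 to 40. Narrow these once the flow-or-pool question is settled, and give the AUROC interval expected at those sizes, above all for IPF versus NSIP.
2. Keep 40 per group and state a recruitment period consistent with the figures. If the flow is of new patients at 70% consent, this is about 14 to 15 months, set by IPF. If it is a recurring pool, extra time alone does not secure 40, and the source of the additional IPF patients needs to be stated.

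The cost is a change of wording plus either a less favourable stated size or a longer recruitment window. No outcome, analysis or study procedure changes.
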